### Planned Statistical Analyses

The results of a power analysis suggest, that a total of up to 166 patients (83 patients per group) might be needed to detect a significant effect. By applying a group sequential study design the number of patients needed is raised to 180 to allow for interim analyses to be performed after including 60 and 120 patients, respectively. To the best of our knowledge the motor ISA-Assessment has not been applied in a longitudinal study design. Depending on the results of these interim analyses or due to economic reasons, the study might be stopped beforehand.

Demographic and baseline characteristics will be compared using *t* tests or other non-parametric methods, if necessary. To analyze most of the primary and secondary outcomes, performing repeated-measures mixed model analyses of covariance will be essential. Independent variables will be group (intervention and waitlist) and time (pre, post and 8-week follow-up) and also their interaction. Baseline measure, the amount of medication (levodopa equivalent daily dose) and depression scores will be included as covariates. To specifically analyze ISAm scores, which are the main outcome, and to determine their degree of objectiveness, inter-rater reliability will be computed for each measurement point in time.

In order to get more insight into possible mechanisms of mindfulness, ISA and their connection to each other, several moderation and mediation analyses are planned. For example, we expect the number of completed training sessions, motor symptom severity and patients’ general cognitive performance level to be possible moderating factors affecting mindfulness scores itself and/or the relationship between mindfulness and ISA. Among others, mediating factors considered will be cognitive performance of sustained attention and questionnaire scores of negative emotions like anxiety and depression. Of course, neurobiological changes will be included as well.

When the effectiveness of a treatment is evaluated, the question of how to deal with dropout patients has to be considered. If a patient cannot conclude his or her study participation, the reason and time of drop out will be documented. To still be able to include as many patients as possible in the analyses, the intention-to-treat analysis is preferred. For missing values, missing at random-analyses will be performed. In case of positive results, maximum likelihood methods will be applied. Data will be analyzed using SPSS, version 26.0 (IBM Corp., Armonk, NY, United States). To analyze qualitative data collected during semi-structured interviews, qualitative content analysis will be used (Mayring, 2015).

Imaging fMRI data will be analyzed using SPM12 (Penny et al., 2007). Functional connectivity of the left and right anterior insula and the anterior cingulate – central nodes of the salience network which have repeatedly been described to be altered following mindfulness interventions – will be analyzed by comparing pre to post measurements within and between groups, focusing on connectivity with the medial prefrontal cortex and the default mode network (Kilpatrick et al., 2011; Doll et al., 2015). Voxel-based morphometry will be applied to perform pre-post between-group comparisons of gray matter density in the same regions. Diffusion MRI will be used to analyze training effects on fractional anisotropy of the anterior-superior parts of the corona radiata and corpus callosum, following results reported after a similar intervention in healthy subjects (Tang et al., 2010). Neural correlates of impaired self-awareness (motor and cognitive) will be assessed based on previous findings in FDG-PET, with the cingulate gyrus and right insular cortex as regions of interest in morphometric and functional connectivity analyses.

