### Study Design

To evaluate the effectiveness of IPSUM on ISAm an adaptive pre-post-design is applied. First, eligible patients are randomized into an intervention group and a waitlist control group. After approximately eight to twelve patients have been successfully recruited, they are randomized by a computer program. Patients of the intervention group are measured at three points in time: before, directly after and 8 weeks after the intervention has ended. As stated before, the intervention takes place between the first two measurements and continues for 8 weeks. Patients of the control group are measured at the same time intervals, but do not take part in the intervention and are therefore treated as usual. For ethical reasons those patients can participate in the intervention after the study has ended. Figure 1 gives an overview of the course of the study.

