### Intervention Protocol

IPSUM is an 8 weeks long, group-based intervention which seeks to improve mindfulness and self-awareness of motor symptoms in patients with PD. In this study, all training sessions are held by a psychologist (main author [name]). The concept is designed for groups of 4–8 patients and consists of 8 weekly sessions of approximately 2 h of duration. The main topic of a session differs from week to week. Table 2 gives an overview of all weekly topics.

**TABLE 2 T2:** Session Overview.

Week	Topic	Main goal
1	Introduction to the concept of mindfulness	Understanding the general concept in theory and by practice
2	The power of breathing	Understanding that we can only control our behavior (e.g., by experiencing the importance of breathing)
3	Thoughts and appraisals	Introduction to the concept of defusion from one’s own thoughts and appraisals and the importance of observing them
4	How to deal with emotions	Learning about the purpose of pleasant and unpleasant emotions and ways of self-care
5	Stabilization of mindful practice	Repetition of previously gained knowledge as well as solving current problems with daily practice
6	Mindfulness and stress resilience	Learning about the use of mindfulness techniques in regards of stress reduction
7	Moving meditation	Performing the complete sequence of sitting yoga composed of movements learned during the training
8	Closing session: A new beginning	Evaluation of the whole training participation and to find solutions for persisting problems of mindful practice to facilitate independent practice after the intervention has ended

While each session’s general topic is different, various recurring elements can be highlighted. For once, each week contains of a short theoretical input which fits the weekly topic. To account for possible impairment of attention, concentration or general cognition, this aspect will not exceed a duration of 15 min. A practical exercise which builds on the theoretical input is performed.

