Starting in week two, each session will begin with a reflection of the week before. Here, the patients get the opportunity to talk about their experiences with the previous week’s homework and possible difficulties they might have encountered. The group setting is expected to be quite helpful for sharing common experience among the patients and getting support to overcome possible problems that may arise during daily practice. At the end of each session, each patient receives a brief written summary containing all relevant information of the theoretical input to allow reviewing specific details of the newly learned information as needed and to support independent practice at home. To continue mindfulness training at home, patients are asked to further practice 30 min of daily mindfulness meditation in addition to improving their informal mindful practice. To ensure compliance, patients are asked to note down all performed mindfulness exercises in tables contained in their written summary for another 8 weeks.

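### The stated primary model has no term for the training groups in which IPSUM is delivered, so its standard error is too small if outcomes correlate within those groups

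*Protocol article*

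**What the plan says.** **Delivery.** Under Intervention Protocol: "The concept is designed for groups of 4–8 patients and consists of 8 weekly sessions of approximately 2 h of duration". The same section says "In this study, all training sessions are held by a psychologist" and, on the group itself, "The group setting is expected to be quite helpful for sharing common experience among the patients".

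**Randomisation and control arm.** Under Study Design: "After approximately eight to twelve patients have been successfully recruited, they are randomized by a computer program". The same section states that waitlist patients follow the same assessment schedule, receive usual care and attend no training. Clustering by treatment group can therefore arise in one arm only.

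**Model.** Planned Statistical Analyses names a repeated-measures mixed-model analysis of covariance: "Independent variables will be group (intervention and waitlist) and time (pre, post and 8-week follow-up) and also their interaction". The covariates are the baseline value, levodopa equivalent daily dose and depression score. No random effects are listed.

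**Sample size.** The power analysis suggests that "a total of up to 166 patients (83 patients per group) might be needed". This is raised to 180 to allow interim analyses after 60 and 120 patients. Clustering, an ICC or a design effect is not mentioned anywhere in the article.

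**The concern.** Patients who train together for 8 weeks, share experiences and support each other may end up more alike than patients from different training groups. The article itself expects the group to help. If so, the intervention-arm mean varies more than its patient count suggests, and a model without a training-group term does not see this. The test of the primary outcome, change in the motor self-awareness score from baseline to post-intervention, would then reject too often. Its confidence interval would be too narrow, and the planned sample would carry less information than the count implies.

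The batch is a separate matter. Each batch supplies patients to both arms, so leaving it out of the model costs precision; it does not inflate the type I error.

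**Working it through.** **Inputs from the article.** Training groups of 4–8; batches of about 8–12; 83 patients per arm, hence 1:1 allocation; total 166, raised to 180.

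**Assumptions.** Two-sided alpha 0.05, one training group per batch, and ICC 0.01, 0.05 or 0.10. The article gives no alpha, power or ICC. An equal split of a batch yields 8/2 = 4 to 12/2 = 6 intervention patients, so m = 4–6 is used.

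**The plan's own figure.** 166 cannot be reproduced, because effect size, SD, power and dropout are not shown. Under independence, 83 per arm corresponds to d = √(2/83) × (1.960 + 0.842) = 0.435 at 80% power, or √(2/83) × (1.960 + 1.282) = 0.503 at 90%. Some settings with a dropout allowance also fit, so the inputs cannot be identified. The step 180/166 = 1.084 lies between three-look O'Brien-Fleming (about 1.02) and Pocock (about 1.15–1.16) inflation. Interim looks alone can therefore explain it.

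**Training-group clustering in one arm.**
- Design effect in the intervention arm: DE = 1 + (m − 1) × ICC
- Variance ratio of the arm difference: VR = (1 + DE)/2
- True/reported standard error = √VR
- Actual alpha = 2 × [1 − Φ(1.96/√VR)]
- Effective N = 180/VR

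| ICC | m | DE | VR | √VR | Actual alpha | Effective N of 180 | Power if 166 gave 80% |
|---|---|---|---|---|---|---|---|
| 0.01 | 4 | 1.03 | 1.015 | 1.007 | 5.2% | 177 | 79.4% |
| 0.01 | 6 | 1.05 | 1.025 | 1.012 | 5.3% | 176 | 79.0% |
| 0.05 | 4 | 1.15 | 1.075 | 1.037 | 5.9% | 167 | 77.1% |
| 0.05 | 6 | 1.25 | 1.125 | 1.061 | 6.5% | 160 | 75.2% |
| 0.10 | 4 | 1.30 | 1.150 | 1.072 | 6.8% | 157 | 74.3% |
| 0.10 | 6 | 1.50 | 1.250 | 1.118 | 8.0% | 144 | 70.7% |

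**Adding variance shared by the batch.** Let g be the training-group share and b the batch share of the total variance. The batch effect cancels from the within-batch arm difference, while the naive variance still contains it. Hence

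VR ≈ [m·g + (1 − g − b) + (1 − b)]/2 = 1 + (m − 1)g/2 − b.

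With g = b = 0.05:
- m = 4: 1 + 0.075 − 0.05 = 1.025, alpha 5.3%
- m = 6: 1 + 0.125 − 0.05 = 1.075, alpha 5.9%

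A simulated two-sample t-test (20,000 runs, 88–90 patients per arm) gave 5.3% at m = 4, 6.1% at m = 6 and 6.7% at m = 8. With batch variance alone and b = 0.05, simulated alpha was 4.4–4.7%, below nominal. The inflation disappears only if b reaches (m − 1)g/2, that is 1.5g at m = 4 or 2.5g at m = 6.

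**Number of training groups.** With 90 intervention patients: 90/6 = 15 to 90/4 = 22.5, so about 15–22. At the first interim look (60 patients, 30 of them in the intervention arm): 30/6 = 5 to 30/4 = 7.5.

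**The case against.** **The random effects may exist.** The article is a condensed account and names a mixed model. The factors and covariates it lists are fixed effects, and a training-group random effect could stand in a full plan that is not shown. A reader might infer that the plan declares all patients independent; the article does not say so. What remains is that it spells out the primary model's factors and covariates and names no level above the patient. Followed as written, that model ignores the training group.

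**166 may already contain an allowance.** A reader might infer that 166 assumes independence. It is compatible with that, but its inputs are not shown, so this cannot be established. Only the step from 166 to 180 has a stated reason, and that reason is the interim looks.

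**Batching works the other way.** A reader might link randomisation in batches to standard errors that are too small. The opposite holds, and this objection stands in full.

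**The effect may be small.** No ICC is given, and one psychologist leads every session, so no between-therapist variance arises. Much of the practice is done at home. Expected mutual support makes correlation plausible but does not show it for a rater-scored outcome. At ICC 0.01 the effect is negligible.

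**Groups of eight.** The delivery format allows up to 8, where alpha would reach 7.1% (ICC 0.05) or 9.2% (ICC 0.10). Batches of about 8–12 split equally do not produce groups of that size, and the article describes no pooling of batches. Those figures should not be used as the expected size.

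**Conclusion.** The point holds conditionally. The model as stated makes no allowance for training-group clustering in the intervention arm, and it understates the standard error of the arm effect if training groups differ. At 4–6 patients per group, and before any offset from batch variance, the true standard error is about 1% (ICC 0.01), 4–6% (ICC 0.05) or 7–12% (ICC 0.10) larger than reported. Shared batch variance reduces the inflation: with both shares at 0.05, simulated alpha is about 5.3–6.7% for groups of 4–8.

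These sizes rest on assumed ICCs, 1:1 allocation, one training group per batch and a simple two-arm comparison in place of the full repeated-measures model. The documents do not support saying that the standard errors are certainly too small. This is a modest weakness in the primary analysis that is cheap to remove; it does not undermine the design.

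**What to change.** Before outcome analysis:

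1. Specify a partially nested mixed model. Put a random training-group effect in the intervention arm only, acting on the post-baseline assessments, and treat each waitlist patient as a singleton.
2. Include randomisation batch as a stratum effect, which recovers the precision available from allocation within batch.
3. Use Satterthwaite or Kenward-Roger degrees of freedom, at the interim looks as well, where only about 5–7 training groups would contribute at 60 patients.
4. Give the inputs behind 166, say whether they include clustering, and report what 166/180 patients deliver over ICC 0–0.10. This does not require enrolling more patients.

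**Cost.** Training-group and batch identifiers in the data set and a few lines of model syntax. Intervals become slightly wider and the degrees of freedom fall, since the intervention arm supplies only about 15–22 training groups.

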### Outcome Measures

The main goal of this study is to increase self-awareness for motor symptoms. Therefore, the primary outcome for efficacy testing is a global ISAm-score. To be precise, mainly its change from baseline to post-intervention assessment is analyzed to evaluate the effectiveness of IPSUM. Changes of ISAm from baseline to follow-up are considered as a secondary outcome. However, we determined several other secondary outcomes like general neuropsychological test performance, the congruence between neuropsychological test performance and subjective daily life impairment (ISAc) and the congruence between objective neuropsychological test performance and subjective test performance (metacognition). Also, changes of several PD related symptoms (depression, apathy, impulsivity, sleeping problems) and affective states (stress, anxiety, quality of life, mindfulness) are analyzed. The aforementioned secondary outcomes comprise all changes from baseline to post measurement as well as changes from baseline to follow-up measurement. Additionally, structural neurobiological changes in the Insula and Cingulate Cortices, as well as any kind of reported subjective changes during the semi-structured interview are also considered when IPSUM’s effectiveness is evaluated.

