### Questionnaires

To evaluate the effects of IPSUM on emotional well-being as well as other non-motor symptoms of PD, all patients are asked to complete several questionnaires. All questionnaires are filled out at all three measurement points. PD related symptoms of interest are depression [BDI-2], Apathy [Apathy Evaluation Scale – AES (Marin et al., 1991)], Impulsivity [Questionnaire for Impulsive-Compulsive Disorders in PD – QUIP (Probst et al., 2014)] and Sleeping Problems [Parkinson’s Diseases Sleep Scale-2 – PDSS-2 (Trenkwalder et al., 2011)]. Furthermore, to study changes of emotional well-being, experienced stress [Perceived Stress Questionnaire-20 – PSQ-20 (Fliege et al., 2005)], state and trait anxiety [State-Trait Anxiety Inventory – STAI (Spielberger, 2010)] and quality of life [Parkinson’s Disease Quality of Life – PDQ-39 (Berger et al., 1999)] are assessed. Data about subjective cognitive impairment in general [CFQ] and specifically for executive function [DEX] is needed to evaluate ISAc, as described above. Since this study intends to evaluate the effects of a mindfulness based intervention, trait mindfulness [German Version of the Five Facet Mindfulness Questionnaire – FFMQ-D (Marin et al., 1991; Michalak et al., 2016)] is also assessed.

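### The pre-score is both a response level and a covariate, so the planned baseline adjustment adds no precision to the primary baseline-to-post contrast

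*Protocol article*

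**What the plan says.** Outcome Measures defines the primary outcome through the global ISAm score: "mainly its change from baseline to post-intervention assessment is analyzed to evaluate the effectiveness of IPSUM". The later change is ranked below it: "Changes of ISAm from baseline to follow-up are considered as a secondary outcome".

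Planned Statistical Analyses gives one model for most outcomes: "To analyze most of the primary and secondary outcomes, performing repeated-measures mixed model analyses of covariance will be essential". Its factors follow: "Independent variables will be group (intervention and waitlist) and time (pre, post and 8-week follow-up) and also their interaction". The next sentence gives the covariates: "Baseline measure, the amount of medication (levodopa equivalent daily dose) and depression scores will be included as covariates". Group-by-time is the only interaction named. No contrast is singled out as the primary test, and the visit at which the medication and depression covariates are taken is not given.

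On depression, the Questionnaires section says "All questionnaires are filled out at all three measurement points". Depression is also among the secondary outcomes, and among the candidate mediators: "mediating factors considered will be cognitive performance of sustained attention and questionnaire scores of negative emotions like anxiety and depression".

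**The concern.** Baseline can enter a longitudinal model as a response or as a covariate. The section asks for both. A covariate that takes the same value at every visit explains differences between patients. The primary question is about change within patients compared between groups, and a main-effect covariate does not reach that comparison. The plan then has the form of an ANCOVA but delivers a change-score analysis.

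What is at stake is precision. ISAm has not been used longitudinally before, its pre-post correlation is unknown, and the article allows for stopping before 180 patients. Precision that can be had free is worth keeping in that setting.

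A smaller, related question is which depression score is meant. A baseline score is a sound covariate. A score taken after randomisation is not, because depression may itself respond to the intervention.

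**Working it through.** **Inputs from the article.** Three visits; group, time and group-by-time; baseline score, levodopa equivalent dose and depression as covariates; 83 per group (166 in all) for the fixed design, raised to 180 for interim analyses. Alpha, sidedness, power, effect size, SD and pre-post correlation are not given.

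**The plan's own figure.** The 166 cannot be reproduced from the article. It can only be solved backwards: d = (z_alpha + z_power) × √(2/83). Two-sided 5% and 80% power give d = (1.960 + 0.842) × 0.1552 = 0.435. At 90% power d is 0.503. One-sided 5% gives 0.386 and 0.454. The figure is neither confirmed nor refuted. Below, d = 0.435 in units of the SD of a single score is an assumption.

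**Why the covariate cancels.** Let X be the patient's pre-score, with coefficient c. The model is

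Y(visit) = group + time + group×time + c·X + patient effect + error.

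Subtracting pre from post removes both c·X and the patient effect. With complete data and compound symmetry, the group-by-time estimate for post minus pre is then the raw difference in mean change. The same algebra removes any other covariate that is constant over visits and enters as a main effect.

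**Simulation** (83 per group, 3 visits, equal correlation ρ, 1000 runs per setting).
- With the baseline main effect, the estimate equalled the change-score difference to about 1e-14 in every run.
- At ρ = 0.5 its standard error was 0.154 with the covariate and 0.154 without. ANCOVA gave 0.135.
- With a true effect of −0.435 at ρ = 0.5, the mean estimate was −0.436 from the model as specified and −0.439 from ANCOVA, so neither is biased.
- With no true effect, rejection rates lay between about 4% and 7% over all settings.

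**Size of the loss.** The variance of the change-score contrast is proportional to 2(1−ρ), and that of ANCOVA to 1−ρ². The ratio is (1−ρ²)/[2(1−ρ)] = (1+ρ)/2. Power is Φ(d/√(2V/83) − 1.96), where V is the variance factor.

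| Assumed ρ | V, change | V, ANCOVA | Ratio | 166 × ratio | Power, change | Power, ANCOVA | n per group for 80%, change / ANCOVA |
|---|---|---|---|---|---|---|---|
| 0.3 | 1.40 | 0.91 | 0.65 | 108 | 66% | 84% | 117 / 76 |
| 0.5 | 1.00 | 0.75 | 0.75 | 125 | 80% | 90% | 83 / 63 |
| 0.7 | 0.60 | 0.51 | 0.85 | 141 | 95% | 98% | 50 / 43 |

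The fifth column is the number of patients with which ANCOVA would match the precision of 166 under the change-score contrast.

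**Depression covariate (illustration).** Assume an effect on depression of −0.4 SD, a slope of ISAm on depression of 0.3 and a total effect of −0.435. The mean estimate was −0.428 both with baseline depression and with no depression covariate. With the concurrent score it shrank to −0.358.

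**The case against.** **The cancellation depends on an unstated detail.** This is the strongest reply. If a baseline-by-time term is fitted, the estimate equals the ANCOVA estimate (to about 1e-14 in the simulation), and a condensed article may leave such a term to the SAP. That stands as a limit on the claim. Still, the article names one interaction, and it is not that one. The remedy is also untidy while pre stays a response. The pre residual is then exactly zero, and a compound-symmetry fit pools it with the others. That inflates the model variance by 2(2+ρ)/[3(1+ρ)], so the standard error is too large by about 9%, 5% and 3% at ρ = 0.3, 0.5 and 0.7.

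**No shortfall is shown.** This also stands. The 166 may already rest on a change-score or interaction test. At ρ = 0.5 and the assumed d, the specified model has the assumed 80% power.

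**Stronger readings.** A reader might infer three further faults that the article does not support.
- *The primary estimate is biased or invalid.* It is not. The post-minus-pre contrast is the primary quantity in Outcome Measures.
- *The primary test is the two-degree-of-freedom group-by-time interaction, which mixes in follow-up.* The section lists model terms and does not name that test as primary, while Outcome Measures ranks post above follow-up. Nor would it always lose power. Where the one-degree test has 80% power and the two change scores correlate 0.5 (both assumed), the joint test has 71% if the follow-up effect is half the post effect, and 83% if it is fully sustained.
- *Adjusting for depression or medication removes part of the effect.* That would need post-baseline values, and no section says they are used. Medication is described as registered before baseline, and the depression score is also an entry criterion. Mediation is planned as a separate analysis.

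**Conclusion.** The point holds as a loss of precision. As specified, with baseline a main effect and group-by-time the only interaction, the covariate does nothing for the primary contrast. The analysis has 65%, 75% or 85% of the efficiency of ANCOVA at ρ = 0.3, 0.5 or 0.7. Those correlations are assumed, as are the effect size, alpha and power behind the power columns. The exact cancellation was shown for compound symmetry and complete data.

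The timing of the depression and medication covariates is an ambiguity to clear up and not a demonstrated error. It deserves a sentence because depression is measured at every visit and also serves as an outcome and a candidate mediator.

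Severity: should-fix.

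**What to change.** Replace the model sentences in Planned Statistical Analyses with one of two specifications:

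- Responses at post and follow-up only, with group, visit, group-by-visit, baseline score, baseline-by-visit, baseline levodopa equivalent dose and baseline BDI-II; or
- pre, post and follow-up as responses, with the baseline means constrained equal between groups and the pre-score dropped as a covariate.

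Name the one-degree-of-freedom adjusted group difference in ISAm at post as the primary test, and the follow-up difference as secondary. This matches Outcome Measures.

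State that the medication and depression covariates are baseline values, and keep later values for the mediation or descriptive analyses. When BDI-II is the outcome, adjust only for its own baseline.

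The cost is one paragraph. No new data are needed, the first specification runs in the mixed-model procedure of SPSS, and the change is best made before the first interim analysis.
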